### Study population

Study staff identify new TB index cases (ICs) through the National Tuberculosis Elimination Programme (NTEP). Inclusion criteria are: (1) Age ≥ 18 years; (2) New sputum-smear positive (≥ 1+ acid fast bacilli [AFB]) pulmonary TB that is culture or GeneXpert positive; (3) No history of TB treatment; (4) Have at least one household contact (HHC) with whom they shared a house during the previous month; (5) Agree to have HHCs contacted. Exclusion criteria include: (1) Pregnant; (2) No GeneXpert or culture confirmation and unable to provide sputum sample; (3) No HHCs; (4) Known MDR or XDR TB; (5) BMI < 14 kg/m^2^ as to avoid refeeding complications; (6) Kwashiorkor, lower extremity edema or lower extremity neuropathy in those with BMI < 14.

Inclusion criteria for HHC include: (1) Age 18–60 years; (2) Housemate of an eligible TB case for at least the past month; (3) HIV seronegative or willing to be tested; (4) Willing to be tested for pregnancy. Exclusion criteria include: (1) Pregnant at enrollment; (2) Having known diabetes mellitus or evidence by hemoglobin A1C (HbA1c) > 6.5%; (3) GeneXpert positive among those able to produce sputum; (4) History of TB disease; (5) Karnofsky score ≤ 10 (moribund); (6) If BMI < 16 kg/m^2^, abnormal potassium, magnesium, or phosphorus; (7) Kwashiorkor; pitting edema; neuropathy [23].

All HHCs in the home are approached for enrollment. All eligible household contacts in one house are enrolled for prospective follow up if the HHCs fall in overlapping study arms. If there are more than one eligible HHCs, but no overlapping study arm designations, any malnourished HHC screened is enrolled to limit selection bias. We expect to enroll 760 HHCs to identify 120 study participants for longitudinal follow-up. Sample size was determined by participant data from the Regional Prospective Observational Research for Tuberculosis (RePORT India) cohort study [24].

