### Longitudinal follow-up

HHCs that are QFT-Plus positive are placed in one of four study arms for longitudinal follow-up over 2 years (30 in each): (1) Undernourished (BMI < 18.5 kg/m^2^) with parasitic infection (UP); (2) Undernourished without parasitic infection (U); (3) Well-nourished with parasitic infection (WP) and (4) Well-nourished without parasitic infection (W). The field team will attempt to enroll participants evenly across all study arms until target numbers in each arm are met. If enrollment challenges are presented, we will extend the enrollment period by 1 year. Study staff make all attempts to retain each participant in the study via training in rapport building and behavior change as well as having frequent contact through study visits. However, participants are free to discontinue participation at any point.

Participants are evaluated at 7 additional time points after enrollment (2 weeks and months 1, 3, 6, 12, 18 and 24) to monitor change in health status and evaluate change in immune response. All HHCs are screened for TB symptoms at every visit. If a HHC develops TB symptoms at any visit, sputum, blood, and stool samples are collected and the HHC is referred to NTEP for evaluation. Participants who cannot be reached after three contact attempts (on varying days and times) are moved off study and considered lost to follow up. Case report forms assess potential adverse reactions to the intervention, and study staff are trained to report any adverse event to the Principle Investigators (PIs) who determine the correct reporting path to their respective review boards.

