### Nutritional intervention

Undernourished participants are re-consented and enrolled into the study intervention (food and micronutrient supplementation) for 6 months followed by an additional 18-months of extended follow-up. In order to encourage adequate nutritional intake, even in the context of food sharing, the nutrition intervention food rations provided are sufficient to feed all household members. At enrollment, participants are asked the number and age of household members.

The kcal requirements for the food supplements were derived from the Indian TB Nutrition Guidelines that men and women require 2500 and 2100 kilocalories (kcal) respectively; thus, HHCs receive 2600 kcal each with children 13 years and younger receiving 1300 kcal [39]. The 2600 kcal/day needs were determined based off clinical feeding guidelines of 35–40 kcal/kg for undernourished patients [40] to achieve a BMI level considered optimal (21 kg/m^2^) based on the National Institute of Nutrition (NIN) in India’s recommendation for optimizing health and nutrition. In order to determine the contents of the food ration, we consulted local partners, TB experts in India, and nutritionists to create a meal package that is locally acceptable, suitable for vegan and omnivores, and that gives participants dietary variety without compromising nutritional quality. The meal package is comprised of pulses, white rice, groundnuts, and oil; nutrition calculations were made from standard nutrient analysis based on the *Exchange Lists for Meal Planning*, by the Academy of Nutrition & Dietetics in conjunction with the American Diabetes Association [41] (Table 1). These foods were also selected because they can be easily transported to the participant homes and they do not require refrigeration. Enrolled participants also receive a multiple micronutrient supplement (Life-Extension Two-Per-Day Tablets) [42] which contains over 100% of the RDA for Vitamins A, B6, B12, C, D3, and E.

**Table 1 Tab1:** Tuberculosis: Learning the Impact of Nutrition (TB LION) nutritional intervention package for one adult per day

Food category	Food item	Kilocalories	Protein (g)	Fat (g)
Fat (5 g/day)	Vegetable oil	45	0	5
Pulse (117 g/day)	Red gram, green gram, and black gram	468	23.4	1.5
Grains (325 g/day)	White rice	1301	22.75	2.3
Nuts (143 g/day)	Ground nuts	786	35.75	70.1
Total		2600	81.9	78.8

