The field team visits households every other week to replenish the food, assess food consumption and changes in participant health. During the initial food delivery visit, nutritionists provide study food containers and then weigh each container, taring the scale to accurately account for the weight of container. They then add the calculated amount of each food item and mark each container with a black marker to indicate the fill line. The weight of each respective food container is recorded. Nutritionists return to the household every 2 weeks to evaluate the remaining food and vitamin supplement. The remaining food (for each item) is poured into a tared tray, weighed and recorded. Using the initial calculated food quantity and remaining quantity, nutritionists calculate the amount of food consumed by the household and the amount required to replenish the stock which is added to the container before the remaining food to minimize food expiry.

Severely undernourished participants (BMI 14–16) receive partial supplementation for the first 2 weeks of intervention; 30% for the first week and 50% the second week. By the third week, participants will receive 100% of the supplementation. Study staff assess electrolytes (potassium, magnesium, and phosphorus) and conduct an assessment for food consumption and changes in participant health before replenishing the week’s food supply. If electrolyte results are normal, food supply is increased; however, if food is not being consumed based on observation, a second week of the partial ration is provided and electrolytes re-checked. If electrolyte results are abnormal, food supplementation is stopped, and the participant is referred to the hospital. HHC bi-weekly visits detailed above will begin once 100% of the ration is received.

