### Specimen handling and storage

Plasma, serum and whole blood are collected serially over 1 year (Additional file 1: Table S1). Testing is performed for complete blood count (CBC), albumin, C reactive protein (CRP), HIV, and Hemoglobin A1c; for severely malnourished IC and HHC, electrolytes (potassium, magnesium, and phosphorus) are measured. Additional serum samples are aliquoted and frozen. QFT-Plus (QIAGEN, Germany) testing is performed and analyzed as per package instructions; supernatant is extracted and stored at − 80 °C. Tuberculin skin tests (TST; ARKRAY, USA) is administered upon screening and repeated at six months if initial TST was negative (< 5 mm) [45]. Whole blood is collected in PAXgene tubes for RNA extraction and stored at − 80 °C. For isolation of PBMCs, whole blood is collected in Sodium Heparin and K2 EDTA (BD Biosciences) tubes. Plasma is harvested prior to whole blood dilution for PMBC processing. Blood is diluted in PBS and processed using Ficoll-Plaque density gradient media to isolate PBMCs. Following cell count, 5–10 × 10^6^ PBMCs is aliquoted into cryovials in fetal bovine serum (FBS) containing 10% dimethyl sulfoxide (DMSO), stored overnight at − 80 °C and then transferred to liquid nitrogen for long-term storage. The remaining plasma is stored at − 80 °C. Stool samples are collected (as described above). Plasma and serum is collected in K2 EDTA-10.8 mg tubes, wrapped in aluminum foil for light shielding, and stored at − 80 °C for future micronutrient testing. Sputum samples are processed (as described above) and stored in cryo-containers at − 80 °C. Urine samples are assessed for pregnancy using urine spot tests. Field and laboratory staff are trained in and follow strict sample collection, transportation and storage protocols.

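### As printed, a household contact with BMI below 14 and normal electrolytes goes straight to the full ration, because the stepped start covers only BMI 14–16

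*Protocol article*

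**What the plan says.** All the relevant text is in the protocol article.

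- **Study population, index cases.** One numbered exclusion is "BMI < 14 kg/m^2^ as to avoid refeeding complications".
- **Study population, household contacts.** No exclusion sets a lower BMI limit. The last two items, which carry the nutritional safeguards, read "If BMI < 16 kg/m^2^, abnormal potassium, magnesium, or phosphorus; (7) Kwashiorkor; pitting edema; neuropathy".
- **Longitudinal follow-up.** The undernourished arms have an upper BMI limit only; one of them is "Undernourished (BMI < 18.5 kg/m^2^) with parasitic infection (UP").
- **Nutritional intervention, default ration.** Undernourished participants enter the food intervention, where "HHCs receive 2600 kcal each with children 13 years and younger receiving 1300 kcal".
- **Nutritional intervention, exception.** "Severely undernourished participants (BMI 14–16) receive partial supplementation for the first 2 weeks of intervention", namely "30% for the first week and 50% the second week", with the full ration by the third week. The same paragraph has staff check potassium, magnesium and phosphorus before the week's supply is replenished, and stop feeding and refer if results are abnormal. It adds that "HHC bi-weekly visits detailed above will begin once 100% of the ration is received".
- **Specimen handling and storage.** "for severely malnourished IC and HHC, electrolytes (potassium, magnesium, and phosphorus) are measured". No BMI cut-off, timing or ration rule is attached to this.

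**The concern.** The article names BMI 14 as the point below which refeeding is too risky for an index case, and gives contacts at BMI 14–16 a reduced start with laboratory checks. Neither protection is written for a contact below 14. Applied literally, the rules reverse direction at that threshold: a contact just under 14 starts on more food, with fewer stated checks, than one just over it.

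The stake is the safety of a small number of very thin participants, on a risk the article itself identifies. No estimate, test or arm definition depends on it.

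**Working it through.** **Eligibility and ration by BMI band**

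Take a household contact with normal potassium, magnesium and phosphorus, no kwashiorkor, pitting edema or neuropathy, and all other criteria met.

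| BMI | Excluded as a contact? | In an undernourished arm? | Ration rule that applies |
|---|---|---|---|
| 16 to below 18.5 | No | Yes | Default, 2600 kcal/day |
| 14–16 | No | Yes | 30%, then 50%, then 100%, with electrolyte checks |
| Below 14 | No (the floor is in the index-case list only) | Yes | None specific, so the default, 2600 kcal/day |

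The last row is an inference. The article gives no schedule for contacts below 14, so the default for undernourished participants is the only rule left.

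**The article's own figure**

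The energy column of Table 1 gives 45 + 468 + 1301 + 786 = 2600 kcal per adult per day, which matches the stated total.

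**Size of the difference (one adult's ration)**

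- Stepped, week 1: 0.30 × 2600 = 780 kcal/day
- Stepped, week 2: 0.50 × 2600 = 1300 kcal/day
- Unstepped, both weeks: 2600 kcal/day
- Ratio in week 1: 2600 / 780 = 3.33
- Ratio in week 2: 2600 / 1300 = 2.00
- First 14 days, stepped: 7 × 780 + 7 × 1300 = 5,460 + 9,100 = 14,560 kcal
- First 14 days, unstepped: 14 × 2600 = 36,400 kcal
- Ratio over 14 days: 36,400 / 14,560 = 2.5

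None of these needs an assumed height or weight.

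**Scale per kilogram (assumed heights)**

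The article gives no heights, so I assume 1.45 to 1.70 m. With weight = BMI × height², at BMI 13.9:

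- Height 1.45 m: 29.2 kg. Full ration 2600 / 29.2 ≈ 89 kcal/kg/day; 30% step 780 / 29.2 ≈ 27.
- Height 1.70 m: 40.2 kg. Full ration 2600 / 40.2 ≈ 65 kcal/kg/day; 30% step 780 / 40.2 ≈ 19.

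The feeding guideline cited under Nutritional intervention is 35–40 kcal/kg. The ration was set to reach a target BMI of 21, so some excess at a lower current weight is expected. At BMI 16 the full ration is still about 56–77 kcal/kg/day over the same heights. The stepped start holds this back at first for contacts at BMI 14–16 and, as printed, not for those below 14.

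**Monitoring**

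At BMI 14–16, electrolytes are checked before each weekly increase. On the full ration, the stated schedule is a visit every second week, with no electrolyte re-check attached.

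**The case against.** The strongest reply is that this is a journal article and the missing floor may be in the full protocol. The band's lower edge of 14 makes most sense if nobody below 14 is fed. The eligibility lists also look loosely compressed: one index-case exclusion concerns clinical signs in people below BMI 14, whom the preceding item already removes. This is a fair account of probable intent and it limits confidence. It does not remove the problem, because the article prints numbered criteria for both populations and a two-sided dosing band, and these do not fit together. Nor is intent settled by the text: the contacts' electrolyte exclusion applies below BMI 16 with no lower edge.

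Four further points were raised.

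- **Day-one full feeding is not stated.** Correct; it follows from the default. Field staff might well treat a contact below 14 as severely undernourished and step the ration anyway, but the only printed definition of that category is BMI 14–16.
- **The calorie figures are supply, not intake.** Correct. Rations are sized for the whole household and food sharing is expected. The ratios restate the 30% and 50% steps and do not estimate refeeding risk.
- **The group is small and may be empty.** Correct. The undernourished arms total 60 (2 × 30), most members will be well above BMI 14, and no BMI distribution is given.
- **Other safeguards remain.** Correct: the baseline electrolyte exclusion, the exclusion for edema and neuropathy, electrolyte measurement in severely malnourished contacts, the two-week visit and adverse-event reporting. But contacts at BMI 14–16 pass the same baseline criteria and are still given a stepped start with re-checks, so the article does not treat a normal baseline as enough.

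**Conclusion.** The point holds as printed and should be fixed. For contacts below BMI 14 the article gives neither a floor nor a stepped ration. Its default supplies 3.3 times the stepped ration in week 1, 2.0 times in week 2 and 2.5 times over the first 14 days.

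The conclusion assumes that the printed household-contact list is complete and that the default ration applies where no exception is written. Confidence is medium, because the full protocol may contain a floor. The number affected cannot be estimated from the article and is probably very small. The consequence is limited to participant safety.

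**What to change.** Add BMI below 14 kg/m² to the household-contact exclusions under Study population. This matches the index-case floor and its refeeding rationale, and makes the 14–16 band under Nutritional intervention complete.

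If the sponsor does intend to enroll contacts below 14, change the band under Nutritional intervention from 14–16 to below 16 instead. Such a contact would then start at 780 kcal/day, move to 1300 and then 2600, with electrolytes checked before each increase.

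If the full protocol already has the floor, confirm that the field teams apply it to contacts.

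The cost is a one-line amendment and a memo to the field teams, plus possibly the loss of a very few contacts under the first option. Sample size and analysis do not change.

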### Data management

Data, for those screened and enrolled, is entered into paper case report forms that are reviewed in person for completion by the study research officer. Each form is manually reviewed for completion and quality control. Incomplete forms are returned to the field team for rectification. Field teams then upload all data into the Research Electronic Data Capture (REDCap), a secure, web-based software platform designed to support research studies, providing an intuitive interface for validated data capture, built-in quality control and assurance checks, and audit trails for tracking data (Vanderbilt University, USA) [43, 44].

Data on the server is verified by reviewing electronic data against paper copies by a designated staff member. The verification process is subsequently used to check that provided responses are valid. Inconsistencies or incomplete forms are returned to the field team for rectification. The study coordinator in Boston will review all data for completion once on the REDCap server and will maintain a query log that is routinely sent to the field team for rectification. Regular data reviews are generated on the REDCap platform and in Statistical Analysis Software (SAS, Cary, NC, USA). All onsite study activity is monitored by the site PIs and study coordinator. Weekly meetings are held to address and rectify any issues that arose during the week.

Any de-identified data and statistical code used for analyses may be made public if required for manuscript publication. The study PIs will evaluate requests and give access to the data for analysis and publication of study results. All PIs and authors will be responsible for reviewing and approving any manuscript before publication.

### Specimen handling and storage

Plasma, serum and whole blood are collected serially over 1 year (Additional file 1: Table S1). Testing is performed for complete blood count (CBC), albumin, C reactive protein (CRP), HIV, and Hemoglobin A1c; for severely malnourished IC and HHC, electrolytes (potassium, magnesium, and phosphorus) are measured. Additional serum samples are aliquoted and frozen. QFT-Plus (QIAGEN, Germany) testing is performed and analyzed as per package instructions; supernatant is extracted and stored at − 80 °C. Tuberculin skin tests (TST; ARKRAY, USA) is administered upon screening and repeated at six months if initial TST was negative (< 5 mm) [45]. Whole blood is collected in PAXgene tubes for RNA extraction and stored at − 80 °C. For isolation of PBMCs, whole blood is collected in Sodium Heparin and K2 EDTA (BD Biosciences) tubes. Plasma is harvested prior to whole blood dilution for PMBC processing. Blood is diluted in PBS and processed using Ficoll-Plaque density gradient media to isolate PBMCs. Following cell count, 5–10 × 10^6^ PBMCs is aliquoted into cryovials in fetal bovine serum (FBS) containing 10% dimethyl sulfoxide (DMSO), stored overnight at − 80 °C and then transferred to liquid nitrogen for long-term storage. The remaining plasma is stored at − 80 °C. Stool samples are collected (as described above). Plasma and serum is collected in K2 EDTA-10.8 mg tubes, wrapped in aluminum foil for light shielding, and stored at − 80 °C for future micronutrient testing. Sputum samples are processed (as described above) and stored in cryo-containers at − 80 °C. Urine samples are assessed for pregnancy using urine spot tests. Field and laboratory staff are trained in and follow strict sample collection, transportation and storage protocols.

### Assessment of intracellular bacterial growth in Mtb-infected macrophages

After banking a sufficient number of specimens, we will begin the detailed immunologic assessments. We will use a rapid and high-throughput Mtb-luciferase based assay in peripheral blood monocyte (PBMC)-derived macrophages to examine the effect of undernutrition and parasitic infections on Mtb growth restriction in vitro. This assay measures Mtb growth in macrophages using recombinant Mtb expressing the whole bacterial lux operon (luxCDABE). This assay will produce measurements in the form of relative luminescence units. PBMC will be infected with Mtb at a multiplicity of infection (MOI) of 5 for a 7-day growth assay. Kinetics of luminescence generated will be monitored daily using a luminometer plate reader. Reading at day 0 and daily measurements of luminescence in the same well will allow for correction of minor variations in the number of input cells from each sample when calculating percent growth of Mtb in macrophages.

### Evaluation of antigen-specific memory T-cells

Several subsets of memory T cells exist, including stem cell memory (T-SCM), central memory (T-CM), transitional memory (T-TM) and effector memory (T-EM). Development of memory CD4^+^ T-cells is critical for protection against TB disease [46] and yet, the impact of undernutrition and parasitic infections on the responsiveness of Mtb antigen-specific T-cells has not been fully explored. In this study, we will characterize Mtb antigen-specific memory T-cell phenotypes and functionality, to broaden understanding of the impact of undernutrition and parasitic infections on these cells, beyond that of IFNγ expression. In addition, the evolving memory T-cell response in undernourished individuals, with and without feeding, will also be examined. We will use multiparametric flow cytometry and use cell surface markers to compare memory T-cell subsets in PBMCs collected from the different groups. Freshly thawed, cryopreserved PBMCs will be stimulated with ESAT-6, CFP-10, and Ag85B in the presence of anti-CD28 and anti-CD49d antibodies for 16 h. To mark the antigen specificity of memory subsets, expression of IFNγ, IL-2, TNFα and IL-17 will be evaluated by intracytoplasmic staining. Expression of PD1, a marker of T cell exhaustion, will be examined in each memory T cell subset. The FLOW cytometry staining panel also includes antibodies reactive against FoxP3 and CD25 to identify Tregulatory (Treg) cells that impact CD4^+^ T-cell proliferation and function.

FLOW Jo software (Tree Star Inc., San Carlos, CA) will be used to analyze the data to obtain frequency of T-SCM, T-CM, T-TM and T-EM cells. To calculate antigen specific T cells within each of the T cell memory subset, we will determine the percentage of cytokine positive cells (single, double and triple producers are grouped together as cytokine positive cells).

#### Sample size calculations

##### RNA-sequencing

We have two studies validating existing (or newly derived) biomarkers in independent cohorts—distinguishing TB vs. latent TB infection (LTBI) (n = 28 and n = 16, respectively) and predicting progression from LTBI to TB disease (n = 16 progressors and n = 11 controls) [47, 48]. Both studies demonstrated that all biomarkers had AUCs > 0.80 and p-values < 0.0001; therefore, our study with n = 30 samples per group is more than sufficient to apply and validate existing biomarkers.

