## Background

Tuberculosis (TB) is one of the most common infectious causes of death worldwide resulting in 1.2 million deaths in 2019 [1]. One-quarter of the world is infected with *Mycobacterium tuberculosis* (Mtb) and 10% of these individuals develop TB over a lifetime [1]. India has a quarter of the global TB burden with 2.64 million cases and 436,000 deaths in 2019 [1]. The Indian government has committed to an 80% TB incidence reduction by 2025 [2]. However, even as the Indian government invests in improved testing, it has not made commensurate efforts in addressing the leading risk factor for the spread of TB in India: undernutrition. This is a critical shortcoming because more than 50% of TB cases in India are attributable to undernutrition [3], and in Puducherry, as many as 61.5% of TB cases in women and 57.4% in men are attributable to undernutrition [4].

Undernutrition is widely prevalent in India—the World Bank reported in 2018 that 14% of India’s total population was undernourished [5] with the National Family Health Survey reporting 22% and 19% of men and women, respectively, with low BMI in 2017 [6]. A recent systematic review found a log-linear relationship between BMI and TB incidence with a 14% decrease in TB incidence with every unit increase of BMI [7]. Furthermore, a longitudinal study in the United States found that having BMI < 18.5 kg/m^2^ is associated with an adjusted hazard ratio of 12.43 for developing TB disease compared to those with BMI ≥ 18.5 kg/m^2^ [8]. In addition, undernutrition is associated with increased risk of TB treatment failure and mortality [9], greater lung involvement in TB disease [10], and risk of drug-associated toxicities despite weight-based dosing [11].

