#### RNA sequencing

RNA will be extracted from our samples and sequencing libraries will be prepared and sequenced on an Illumina sequencer as described in our previous work [50, 51]. We will perform transcriptomic analysis to understand mechanisms of immune modulation by undernutrition and parasitic infections. Data will undergo quality control, aligned to the most recent human reference genome (hg38) using RSubread, and feature counts will be estimated for each gene as in our previous work [50, 51]. We will use the edgeR package to determine differential gene expression based on a false discovery rate cutoff of 0.05. The data will be subjected to the following: (i) Transcriptional modular/network analysis; (ii) GSVA and ssGSEA scoring of multiple existing TB-related gene expression pathways using our TBSignature profiler (https://github.com/compbiomed/TBSignatureProfiler); and (iii) Ingenuity pathway analysis [51]. We will use the differentially expressed gene sets and/or existing biomarker genes to derive a logistic regression model to develop biomarkers of Mtb infection in undernourished HHC and see if these predict TB risk. To address response to nutritional supplementation and parasite treatment, we will apply a mixed model using the dream R package [52] to account for the repeated measures analysis. We will use an FDR threshold of 0.05 to control for multiple comparisons.

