### Study expectations

In this study, we hypothesize that in HHC of adults with active TB, undernutrition and parasitic infection increase the risk of progression to TB disease and alter the immune response. Further, we hypothesize that nutritional supplementation and treating parasitic infections reverse their effect on the immune response. We anticipate observing that undernutrition and parasitic infection are independently and jointly associated with reduced Mtb killing, increased Th2 and Treg response, and TB risk signatures. We expect that nutritional supplementation improves Mtb killing, increase Th1 response, and alters TB risk signatures. Lastly, we anticipate that treating parasitic infection results in the normalization of immune parameters and the resolution of TB risk signature risk.

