## Discussion

The TB LION study allows us to assess an overlooked obstacle for TB elimination in India—undernutrition—and to evaluate the potential role for parasitic infections in the Indian context. There is a paucity of studies that have assessed the impact of undernutrition on the immune response during Mtb infection and more importantly whether these can be reversed with interventions. The TB LION study, with its ample macronutrient and micronutrient supplementation, rigorous monitoring of nutritional intake, and detailed immunologic analyses address these barriers.

One strength of the study is that we address how the impact of undernutrition is modulated by parasitic infections that are common in India. Intestinal parasites can decrease absorption of key macronutrients (e.g., protein) and micronutrients (e.g., zinc) [21]. Parasites may also have a direct effect on risk of TB progression by inducing Th2 responses and weakening Th-1 (and Th17) responses needed to control Mtb [53]*.* Antihelminth treatment in persons with Mtb infection and Schistosoma or Strongyloides coinfection is associated with increased CD4^+^ IFNγ^+^  cells, suggesting improvement in immune response [54], but data are needed to address whether the implications are similar for other parasites. The TB LION study further informs the role of parasitic infection on risk of progression to TB disease, the time course of improvement in these responses after parasite treatment, and the durability of the response. Furthermore, we are able to address the interplay of undernutrition and parasite infections.

The TB LION study is an ambitious study, with potential to yield very meaningful information. We are confident that our design and methodology, with the addition of sample collection to address the impact of potential COVID-19 infection (through serology), provides comprehensive data to draw sound conclusions regarding the risk of progression to active TB among HHCs. Another key strength of this study is the prospective follow up with clinical assessment on all study participants. Extensive data collection on all participants allows for thorough comparative analyses within and across participant groups. We perform a qualitative assessment of the intervention, a cost-effectiveness analysis of nutritional interventions, and assessments of micronutrient contributions to immune response.

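### The claim that 30 per group suffices to validate existing biomarkers is drawn from TB-versus-latent and progressor-versus-control studies, but the groups of 30 here are nutrition-by-parasite arms

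*Protocol article*

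**What the plan says.** **Protocol article, Sample size calculations, RNA-sequencing.** Two earlier studies are cited. One was for "distinguishing TB vs. latent TB infection (LTBI) (n = 28 and n = 16, respectively"); the other was for "predicting progression from LTBI to TB disease (n = 16 progressors and n = 11 controls"). The text adds: "Both studies demonstrated that all biomarkers had AUCs > 0.80 and p-values < 0.0001". From this it concludes that 30 "samples per group is more than sufficient to apply and validate existing biomarkers".

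**Longitudinal follow-up and Study population.** The four groups of 30 are QFT-Plus positive household contacts, classified by BMI below or at least 18.5 and by helminth infection. Contacts with a positive GeneXpert (among those who can produce sputum) or a history of TB are excluded.

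**Statistical analyses, RNA sequencing.** A logistic model is planned to "develop biomarkers of Mtb infection in undernourished HHC and see if these predict TB risk".

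**Study expectations.** The hypothesis includes that "undernutrition and parasitic infection increase the risk of progression to TB disease".

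**Discussion.** The design, it is said, "provides comprehensive data to draw sound conclusions regarding the risk of progression to active TB among HHCs".

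**Background.** The only absolute progression risk given is that "10% of these individuals develop TB over a lifetime". The same section cites an adjusted hazard ratio of 12.43 for low BMI.

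**The concern.** An AUC for separating TB from latent infection, or progressors from non-progressors, describes contrasts in disease state. It does not tell us how far a signature differs between undernourished and well-nourished infected contacts, nor how precisely prediction can be validated in a cohort where few members may progress. Thirty people in an exposure arm are not 30 TB cases or 30 progressors. The article gives no expected number of progressors anywhere.

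At stake is how the results will be read. If the stated sufficiency is taken at face value, an AUC resting on a handful of TB cases could be reported as validation of a risk signature, and a difference of a few cases between arms as evidence on progression risk.

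**Working it through.** **Can n = 30 be reproduced?** No. The paragraph gives no alpha, power, target contrast or formula. I assume two-sided 0.05 throughout.

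**1. Where the stated inference would hold.** I use the Hanley–McNeil variance for an AUC A with n1 cases and n2 non-cases:

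SE² = [A(1−A) + (n1−1)(Q1−A²) + (n2−1)(Q2−A²)] / (n1·n2), with Q1 = A/(2−A) and Q2 = 2A²/(1+A).

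At A = 0.80, Q1 = 0.667 and Q2 = 0.711. If 30 against 30 really were TB against latent, or progressor against control, SE = 0.058, the 95% half-width is 0.11, and power against an AUC of 0.5 is 99.6%. So the claim is sound for that contrast, but it is not the contrast between the trial's arms.

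**2. Expected progressors.** Cases = 120 × two-year risk. The article gives no two-year risk, so 2 to 10% is my assumption.

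| Assumed 2-year risk | Expected in 120 | Expected per arm of 30 | Cases used for AUC | SE at AUC 0.80 | 95% half-width |
|---|---|---|---|---|---|
| 2% | 2.4 | 0.6 | 2 vs 118 | 0.190 | 0.37 |
| 5% | 6 | 1.5 | 6 vs 114 | 0.110 | 0.22 |
| 10% | 12 | 3 | 12 vs 108 | 0.079 | 0.15 |

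Matching the 16 progressors of the cited study needs 16/120 = 13.3%. The binomial chance of at least 16 is 0.03% at 5% risk and 14% at 10% risk. At 5% risk an arm of 30 has a 0.95^30 = 21% chance of no case.

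**3. Power for a nutrition effect on progression, 60 against 60, exact Fisher test.** For a doubling of risk:

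| Well-nourished | Undernourished | Expected cases | Power |
|---|---|---|---|
| 3.3% | 6.7% | 6 | 4% |
| 5% | 10% | 9 | 9% |
| 6.7% | 13.3% | 12 | 14% |

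Now carry over the hazard ratio of 12.43 cited in the Background, with risk in the undernourished = 1 − (1 − p)^12.43:

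| Well-nourished (assumed) | Undernourished | Expected cases | Power |
|---|---|---|---|
| 0.5% | 6.0% | 3.9 | 12% |
| 1.0% | 11.7% | 7.6 | 54% |
| 1.5% | 17.1% | 11.2 | 81% |

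The article gives no effect size for parasite status, so no comparable figure can be derived for it.

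**4. What 30 per arm does support.** For a continuous signature score, two-sample t test, 80% power:
- one arm against another (30 vs 30): standardised difference 0.74;
- a main effect (60 vs 60): 0.52;
- the nutrition-by-parasite interaction, a difference of two differences with SE = 2·SD/√30: (1.96 + 0.84) × 2/√30 = 1.02.

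**The case against.** The strongest reply is that this cohort need not progress rarely or show only a modest effect. The 10% lifetime figure is for infected people in general. These are household contacts of smear-positive cases and half are undernourished by design, so that figure is not a ceiling for them. With the cited hazard ratio of 12.43, power for nutrition reaches 54 to 81% at assumed risks of 1.0 to 1.5% in the well-nourished. This stands. A reader might infer that the trial cannot test the progression hypothesis at all. The documents do not support that: the answer depends on the assumed effect and base rate.

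A second tempting inference is that the logistic model for Mtb infection has no uninfected comparator by design and should be dropped. That also goes too far. About 760 contacts are to be enrolled to find the 120, so QFT-Plus negative contacts exist. The section on the two-month repeat test admits some persistently negative malnourished contacts to follow-up. Whether negative contacts have RNA samples depends on a supplementary table not shown. The comparator is unnamed, not shown to be absent.

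Third, the trial is described as exploratory, progression to TB is not among its four aims, and the Discussion concedes that arms are small. Applying existing signatures and comparing them between arms, which is Aim 2, remains feasible. All true, and it limits the point to validation, risk prediction and the Discussion's sentence on progression. It does not rescue the sufficiency claim, which is stated without that restriction. The next two sample-size paragraphs (re-analysis of a study of 491, and a bootstrap for T-cell markers) give other grounds for 30, but neither names a contrast present in this trial or an expected number of progressors.

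**Conclusion.** The justification is wrong as written for validating biomarkers: its evidence comes from disease-state contrasts, and the groups of 30 are exposure groups without known TB at entry. This mismatch is visible in the text and needs no assumed rate.

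Its size does rest on assumptions. At two-year risks of 2 to 10%, the cohort yields about 2.4 to 12 progressors, and an AUC of 0.80 would carry a half-width of 0.37 down to 0.15. A nutrition effect on progression has 4 to 14% power for a doubling of risk. Power of 54 to 81% needs an effect as large as the cited hazard ratio together with well-nourished risks of 1.0 to 1.5%. The Discussion's promise of sound conclusions on progression is therefore not secured by the design, although a very large nutrition effect might still be detected. Comparison of signature scores between arms is unaffected.

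**What to change.** - **Sample size calculations, RNA-sequencing:** state that 30 per arm supports comparison of signature scores between arms, with 80% power at two-sided 0.05 for standardised differences of 0.74 (30 vs 30), 0.52 (60 vs 60) and about 1.02 (interaction). Call validation and prediction of TB risk exploratory. Give the expected number of progressors and the risk assumed for it.
- **Statistical analyses, RNA sequencing:** keep the logistic model as exploratory and name its uninfected comparator, since the four arms are QFT-Plus positive apart from the repeat-test exception. Make the two-by-two comparison of signature scores the main analysis for Aim 2.
- **Discussion:** replace the claim about progression risk with descriptive reporting of TB cases by arm, with exact confidence intervals.

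The cost is a less favourable stated claim. No participants, visits or assays are added, and no planned analysis is removed.
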